#### 5.1.1 Pre-registration visit (24-34 weeks gestation)

1. Obtain stage 1 written informed consent (annexure 2) to contact patient during the post-partum period and perform OGTT if not already performed as part of routine care.
2. If OGTT is positive, discuss interest in participation, obtain participant contact details, and deliver brief standardised educational program.

#### 5.1.2 Registration visit (3-18 months post-partum)

1. Perform OGTT and measure HbA1c.
2. If OGTT indicates T2DM, refer for care; if OGTT does not indicate T2DM, invite patient to participate in trial, and arrange randomisation visit appointment (could be same day).

#### 5.1.3 Randomisation visit (Week 0)

1. Obtain stage 2 written informed consent (annexure 3).
2. Assess inclusion and exclusion criteria.
3. Record demographic data and medical history.

4. Measure height, weight, waist circumference, and blood pressure.
5. Administer diet and physical activity questionnaires.
6. Record healthcare utilisation since delivery.

#### **5.1.4 Six month visits (Month 6, 12, 18, 24, 30, and 36)**

1. Measure weight, waist circumference, and blood pressure.
2. Determine whether an interim diagnosis of T2DM has been made.
3. If an interim diagnosis of T2DM has been made, obtain confirmatory source documentation. The participants will not be followed up further, and will be discontinued from the study intervention. Data will be censored for these participants.
4. At Months 6, 18, and 30, perform HbA1c. If value is more than 6.5%, then call patient for OGTT.
5. At Months 12, 24 and 36, perform OGTT, unless an interim diagnosis of T2DM has been made, and source documentation is available. Participants who change glycaemic category, but do not develop T2DM, will be followed up.
6. Administer diet and physical activity questionnaires.
7. Record healthcare utilisation since the last study visit.
8. Record any serious adverse events since the last study visit.

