
### **3.8 ECONOMIC EVALUATION**

The economic evaluation will comprise a trial-based component and a modelled evaluation of long-term costs and outcomes. Intervention costs will be based on salaries and training. A within-trial comparison of health care costs (e.g. blood tests, hospital and clinic visits, and medications) will enable estimation of potential cost-offsets associated with the intervention.

As we do not expect an effect of the intervention on survival, the (within-trial-based) incremental cost effectiveness ratio will be determined by average differences in utility observed between treatment arms in the trial. To capture costs and outcomes beyond the trial, a decision-analytic model will be developed to enable long-term morbidity, quality of life and survival to be simulated. The model will specify a number of health states (such as myocardial infarction, stroke, renal failure, type 2 diabetes with and without micro and macro-vascular complications, death and no disease) between which individuals cycle each year over a lifetime. It will draw on the literature and available databases to determine the transition probabilities between health states and the cost and quality of life associated with each. All patients will simulate progression across states until death. Incremental cost per Quality Adjusted Life Year (QALY) gained will be determined by then folding back the model to determine the average costs and outcomes, discounted at appropriate rate, accrued in both treatment arms. Sensitivity analysis will be conducted to determine the robustness of base case estimates to assumptions used in the economic evaluation.

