#### **5.1.5 EOS visit (End of study)**

1. Measure weight, waist circumference, and blood pressure.
2. Determine whether an interim diagnosis of T2DM has been made.
3. If an interim diagnosis of T2DM has been made, obtain confirmatory source documentation.
4. If an interim diagnosis of T2DM has not been made, perform OGTT and measure HbA1c.
5. Administer diet and physical activity questionnaires.
6. Record healthcare utilisation since the last study visit.
7. Record any serious adverse events since the last study visit.

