#### 3.5 Early study discontinuation/Lost to Follow-up

Early termination is captured on the CRF and may be due to one of the following reasons:

- Withdrawal of Informed consent for follow-up visits
- Development of T2DM
- Occurrence of pregnancy
- Unable to contact or unable to follow-up

In case of early termination, a patient was expected to have an EOS visit completed at the time of termination. For those who did not terminate early, EOS visits with at least partial data collection were to be conducted after 1 July 2020.

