## 4.8 Healthcare utilisation

The number of events as well as the number and proportion of participants accessing each service (e.g. hospital, pharmacy, etc.) at least once during the study will be reported overall and by treatment group. Differences in proportions will be tested using Fisher's exact test.

More detailed analyses of healthcare utilisation including costs will be conducted later and are not described in this SAP.

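### Data collection ends at the closing visit once T2DM is documented, so the within-trial cost-offset omits most diabetes care after diagnosis, and the utilisation tables ignore the shortened follow-up

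*Combined protocol and SAP*

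**What the plan says.** **Protocol 5.1.4, item 3.** After an interim T2DM diagnosis with source documents: "The participants will not be followed up further, and will be discontinued from the study intervention". Item 5 treats lesser changes differently: "Participants who change glycaemic category, but do not develop T2DM, will be followed up". Among glycaemic changes, only T2DM ends data collection.

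**SAP 3.5.** Development of T2DM is a listed reason for early termination, and "In case of early termination, a patient was expected to have an EOS visit completed at the time of termination". SAP Table 2 allows women who stopped for T2DM to count as having completed EOS. SAP Table 4 lists T2DM among the reasons for not being assessed at a visit.

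**Protocol 5.1.5.** The EOS visit makes only the glucose tests conditional: "If an interim diagnosis of T2DM has not been made, perform OGTT and measure HbA1c". Weight, waist, blood pressure, questionnaires and serious adverse events are recorded for everyone, as is the instruction "Record healthcare utilisation since the last study visit".

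**Protocol 3.8.** "A within-trial comparison of health care costs (e.g. blood tests, hospital and clinic visits, and medications) will enable estimation of potential cost-offsets". A separate decision model covers costs beyond the trial, with inputs from literature and databases.

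**SAP 4.8 and Table 12.** "The number of events as well as the number and proportion of participants accessing each service" are reported, with Fisher's exact test on the proportions. SAP 4.6 and Table 11 do the same for any use of each medication category. Neither uses follow-up time. SAP 4.8 defers cost analyses to later work.

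**The concern.** In a diabetes-prevention trial the cost-offset is mainly diabetes care avoided. Here the outcome being prevented also closes the record of that care. A woman found to have T2DM at a study OGTT has her closing visit at about that time, so nearly all her later tests, clinic visits and glucose-lowering medication fall outside the data.

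The tables add a second problem. Observation is shortened by the outcome itself, so if the arms differ in T2DM they differ in observed time. Raw counts and ever-use proportions then favour the arm with more T2DM. If the intervention works, the control arm appears to use less care than it did, and the within-trial offset is understated.

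**Working it through.** **What the plan gives.** The documents contain no figure for this loss, so the size is illustrated from the design assumptions: 1414 women, 1:1 (707 per arm), control incidence 20% at 24 months, relative risk 0.65, hence 0.20 × 0.65 = 13% (SAP 2.2 and 2.6). As a check on those inputs, a two-proportion test at two-sided 5% and 90% power needs 589 per arm, 1178 in total; 1178 × 1.20 = 1413.6, which rounds up to the plan's 1414. That calculation has no further bearing here.

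**Assumptions.**
- The 20% and 0.65 are stated for change in glycaemic category. Protocol 3.5 calls 20% reasonable for T2DM as well; applying 0.65 to T2DM is an assumption.
- Every woman would otherwise be followed for T = 2 years, and T2DM onset is exponential.
- Care use is 1 unit per year before T2DM and m units after it. Neither value is in the documents; m is taken from 1 to 3.

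**Person-time lost.** With risk p over 2 years, λ = −ln(1 − p)/2.

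| | Control, p = 0.20 | Intervention, p = 0.13 | Gap |
|---|---|---|---|
| λ per year | 0.1116 | 0.0696 | |
| Mean observed years if cut at onset, p/λ | 1.793 | 1.867 | 0.074 |
| Share of 2 years lost | 10.4% | 6.7% | 3.7 points |
| Found by the month-12 OGTT, 1 − exp(−λ) | 10.56% | 6.73% | |
| Share lost if cut there (1 year of 2) | 5.3% | 3.4% | 1.9 points |
| Woman-years lost per arm if cut there (× 707) | 74.6 | 47.6 | 27.0 |

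The protocol also has HbA1c visits at months 6 and 18 and accepts outside diagnoses, so the truth should lie between the two cut-offs. For control T2DM of 5% to 27% (27% is the 20-month pilot-derived figure in protocol 3.5) at relative risk 0.65, the gap is 0.89 to 5.15 points (onset) or 0.45 to 2.68 points (month-12 OGTT). At relative risk 1 it is 0.

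**Effect on total use, intervention minus control, units per woman.** With d the difference in mean observed years (intervention minus control), the true difference is −d(m − 1) and the observed difference is +d.

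| | d | True, m = 1 | True, m = 2 | True, m = 3 | Observed |
|---|---|---|---|---|---|
| Cut at onset | 0.074 | 0 | −0.074 | −0.149 | +0.074 |
| Cut at month-12 OGTT | 0.038 | 0 | −0.038 | −0.077 | +0.038 |

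If the T2DM rates are swapped between arms, every sign reverses.

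**Dividing by person-time.** Observed use is then 1 unit per year in both arms, a difference of 0. The rate removes the spurious excess but not the missing offset.

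**Against sampling error.** Taking use as Poisson at 1 per year with 707 per arm, the standard error of the difference in mean counts is √[(1.894 + 1.933)/707] = 0.074 for the month-12 cut, so +0.038 is about half a standard error. For the onset cut it is √[(1.793 + 1.867)/707] = 0.072, so +0.074 is about one. For ever-use with the month-12 cut, expected proportions are 1 − [0.1056e⁻¹ + 0.8944e⁻²] = 84.0% (control) and 1 − [0.0673e⁻¹ + 0.9327e⁻²] = 84.9% (intervention): 0.9 points, with a standard error of about 1.9 points.

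**The case against.** Several objections stand.

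- **The closing visit collects data.** A reader might infer that nothing after diagnosis is ever recorded. The EOS visit takes weight and looks back over healthcare use, so care between an outside diagnosis and that visit is captured. Section 5.1.5 and the Table 3 footnote, which drop only glucose testing after confirmed T2DM, can even be read as letting visits continue. SAP 3.5 and Tables 2 and 4 point the other way, so the passages need reconciling.
- **The direction is conditional.** A reader might infer that the comparison is biased against the intervention outright. That holds only if the intervention lowers T2DM and care use does not fall after diagnosis.
- **The cost analysis is deferred.** SAP 4.8 leaves costs to later work. The handling of truncated costs is therefore unspecified rather than wrongly specified, and the decision model has its own T2DM states. Healthcare utilisation is not a listed primary or secondary outcome, and protocol 5.1 commits to minimum data collection.
- **The illustration rests on outside inputs.** The care-use multiplier is assumed. Follow-up varied, with a 12-month minimum; a woman diagnosed at month 12 whose follow-up would have ended then loses nothing.
- **Intention-to-treat and weight.** A reader might infer a breach of intention-to-treat or a biased weight comparison. SAP 3.2 defines intention-to-treat as analysis by randomised group, which stopping collection does not violate. The mixed models keep every woman with a post-baseline value, including closing-visit values, and neither the size nor the direction of a weight bias can be derived from the documents.

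None of this supplies care data after the closing visit or a time denominator for the SAP tables.

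**Conclusion.** The concern holds in a limited form. Collection stops at the closing visit after T2DM, so the within-trial cost-offset leaves out most post-diagnosis diabetes care and would be understated if the intervention lowers T2DM. The unadjusted comparisons in SAP 4.6 and 4.8 are distorted in a known direction for any given effect on T2DM, but only slightly: about 2 to 4 points of person-time at 20% versus 13% over 24 months, or half to one standard error of the count difference under Poisson use. Under the assumed m of 2 to 3 the expected sign of the difference reverses, but an effect of this size would be hard to distinguish from chance. The primary time-to-event analysis is unaffected, because T2DM is an event from every baseline category.

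**What to change.** 1. **SAP 4.8 and Table 12.** Analyse service use as events per person-year, using a count model with log follow-up time as offset, and report follow-up time by arm. Show that follow-up time beside Table 11 too, with a note that medication use is recorded only up to the closing visit. Cost: one paragraph and table edits, no new data.
2. **Protocol 5.1.4 item 3.** Continue utilisation and medication collection to the common EOS after T2DM, by telephone if needed, as the Covid-19 arrangements already allow for visits. Leave the rule on stopping the intervention untouched. Reconcile item 3 with 5.1.5 and the Table 3 footnote. Cost: one sentence and some further contacts for women with T2DM.
3. **Protocol 3.8, where those data do not exist.** This is the likely case: SAP 2.2 schedules all EOS visits by 31 January 2021, and the final SAP is dated 19 March 2021. State that the within-trial offset is truncated at the closing visit, and take post-diagnosis diabetes cost from the decision model. Item 1 alone is not a substitute, since rates do not recover the missing cost. Cost: a short statement, with the model already planned.

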| Healthcare utilisation (hospital, clinics, tests, medications) |                |   | X | X               | X              | X              |
| Serious Adverse Events #                            |                |   | X | X               | X              | X              |

\*OGTT will not be performed if interim diagnosis of T2DM is adequately confirmed by appropriate source documents

^HbA1c from old records (if available)

\$ If HbA1c is  $\geq 6.5\%$ , then an OGTT will be performed.

\*\* Modified Global Physical Activity Questionnaire and Intake 24 Diet recall

# to be filled only when severe adverse event is seen any time after randomisation

From March 25, 2020, due to lockdown measures relating to the Covid-19 emergency, the following changes to participant follow-up have been instituted:

1. All follow-up visits with study participants will be conducted remotely via telephone. This will exclude the ability to collect any data relating to anthropometric measurements, OGTT, HbA1c and vitals (BP and heart rate).
2. All participants who have completed at least 12 months follow-up (and, if randomised to the intervention, have completed all aspects of the intervention) will have an EOS visit scheduled as their next visit.
3. Once lockdown conditions have been lifted, all participants will be scheduled for a visit to, at a minimum, undergo testing for HbA1c and undergo an OGTT. If conditions allow, in-clinic visits will be arranged for anthropometric measures and vitals (BP and heart rate).

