## **5.3 OUTCOME ADJUDICATION**

As the primary outcome is entirely dependent on changes in absolute values from oral glucose tolerance tests (and does not involve any other non-laboratory criteria), independent outcome adjudication will not be required. To ensure the accuracy of relevant data, 100% source data verification against laboratory reports will be undertaken by appropriately qualified central study staff who are blinded to intervention allocation.

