## 2.6 Sample Size

A sample size of 1414 women with GDM will provide 90% power ( $2\alpha=0.05$ ) to detect a relative risk of 0.65, assuming that the control group cumulative incidence for change in glycaemic category will be 20% at 24 months and allowing for 20% of missing outcome data.

The initial power calculation was based on a chi-square test comparing two proportions at 24 months; however, to account for various study durations, the primary analysis will consist in a survival analysis of time to change in glycaemic category which is expected to have at least the same power as a comparison of proportions.

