### 4.1 General Principles

Analyses will be performed using SAS Enterprise Guide version 8.3 or higher (SAS Institute Inc., Cary, NC, USA).

All variables will be analysed by descriptive statistical methods. The number of data available and missing data, mean, standard deviation, minimum, quartiles, median, and maximum will be calculated for continuous data. Frequency tables will be generated for categorical data. For categorical variables, the number and percentage of patients with a specific level of the variable will be presented.

All tests will be two-sided with a type-I error rate of 5%. Analyses of the primary outcome (change in category of glycaemia from normoglycaemia to IGT, IFG or T2DM or from IFG or IGT to T2DM) will be unadjusted for multiplicity; however, we will control the family-wise error rate across secondary outcomes using a Holm-Bonferroni correction [2]. No other multiplicity adjustment will be applied.

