### 4.9.2 Survival analysis

Change in glycaemic category for primary outcome as defined in section 2.4.1 will be analysed as a time to event calculated as the number of days between randomisation and the day of the event. For subjects with no event, data will be censored on the day of the last OGTT test results.

Survival by treatment arm will be described using a Kaplan-Meier plot with 95% confidence interval will be reported by treatment arm. If available, median time to event as well as quartiles will be derived from the Kaplan-Meier estimates. Censoring will be done at time of last OGTT test.

A Cox model will be used to estimate the Hazard ratio of the two arms (Intervention compared to Control). The Cox model will include the randomised group as well as prior use of insulin as fixed effects and study site as a random effect [4]. We will visually assess the proportional hazard assumption. SAS Proc PHREG will be used.

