**Table 8. Change in glycaemic status**

| Outcome / analysis                  | Intervention
N=xxx | Control
N=xxx    | Hazard/rate
Ratio (95% CI) | p-value |
|-------------------------------------|-----------------------|---------------------|-------------------------------|---------|
| Change in glycaemic category |                       |                     |                               |         |
| Using OGTT only              | xx events      | xx events    |                               |         |
| Survival analysis       | x.xx (x.xx to x.xx)   | x.xx (x.xx to x.xx) | x.xx (x.xx to x.xx)           | 0.xxx   |
| Adjusted                            |                       |                     | x.xx (x.xx to x.xx)           | 0.xxx   |
| Poisson regression                  | x.xx (x.xx to x.xx)   | x.xx (x.xx to x.xx) | x.xx (x.xx to x.xx)           | 0.xxx   |
| Adjusted                            | x.xx (x.xx to x.xx)   | x.xx (x.xx to x.xx) | x.xx (x.xx to x.xx)           | 0.xxx   |
|                                     |                       |                     |                               |         |
| Using HbA1c and FBG          | xx events      | xx events    |                               |         |
| Survival analysis                   | x.xx (x.xx to x.xx)   | x.xx (x.xx to x.xx) | x.xx (x.xx to x.xx)           | 0.xxx   |
| Adjusted                            |                       |                     |                               | 0.xxx   |
| Poisson regression                  | x.xx (x.xx to x.xx)   | x.xx (x.xx to x.xx) | x.xx (x.xx to x.xx)           | 0.xxx   |
| Adjusted                            | x.xx (x.xx to x.xx)   | x.xx (x.xx to x.xx) | x.xx (x.xx to x.xx)           | 0.xxx   |
|                                     |                       |                     |                               |         |
| Development of T2DM          |                       |                     |                               |         |
| Using OGTT only              | xx events      | xx events    |                               |         |
| Survival analysis                   | x.xx (x.xx to x.xx)   | x.xx (x.xx to x.xx) | x.xx (x.xx to x.xx)           | 0.xxx   |
| Poisson regression                  | x.xx (x.xx to x.xx)   | x.xx (x.xx to x.xx) | x.xx (x.xx to x.xx)           | 0.xxx   |

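### Read literally, the protocol and SAP censor as event-free a woman whose first recorded worsening is a documented T2DM diagnosis made outside a study OGTT

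*Combined protocol and SAP*

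**What the plan says.** - **Outcome.** Protocol 3.4 and SAP 2.4.1 and 4.9 count any move from NGT to IFG, IGT or T2DM, or from IFG/IGT to T2DM, up to and including the final visit. Development of T2DM is also a secondary outcome (SAP 2.4.2 and 4.10).
- **Interim diagnosis.** Protocol 5.1.4 item 3 asks for confirmatory source documents, ends follow-up, and states: "Data will be censored for these participants".
- **No test afterwards.** The footnote to protocol Table 3 reads: "OGTT will not be performed if interim diagnosis of T2DM is adequately confirmed by appropriate source documents". Items 5 of 5.1.4 and 4 of 5.1.5 agree with it.
- **Source of the outcome.** Protocol 5.3 gives its reason for doing without independent adjudication: "As the primary outcome is entirely dependent on changes in absolute values from oral glucose tolerance tests". In SAP Table 8 the primary analysis sits under "Using OGTT only".
- **Censoring in the SAP.** Section 4.9.2 states: "For subjects with no event, data will be censored on the day of the last OGTT test results".
- **Censoring in the protocol's statistics section.** Section 3.6 names subsequent pregnancy as the only reason for censoring in the Cox model. It does not mention T2DM.

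**The concern.** Each rule is understandable alone. Together they leave a gap at the event the trial exists to prevent. A woman diagnosed between visits has no study OGTT in the diabetic range, so her last OGTT is non-diabetic and the censoring date falls on or before it.

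Censoring a woman because she has had the event is informative. It could also act unequally by arm. The trial is open-label (protocol 4.2), the intervention arm has regular facilitator contact, and controls are managed by their usual doctor (3.3.2), so diagnosis outside the study may occur at different rates in either direction. There is room for such diagnoses: scheduled OGTTs are 12 months apart, and from 25 March 2020 follow-up was by telephone, without OGTT or HbA1c until lockdown lifted (notes to protocol Table 3).

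**Working it through.** **Step 1. Trace one woman through the rules.**

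| History | Primary outcome, literal text | T2DM outcome, literal text |
|---|---|---|
| T2DM found on a study OGTT | Event | Event |
| NGT at baseline, IFG/IGT on an earlier study OGTT, then T2DM diagnosed outside | Event, at the earlier OGTT | Lost |
| No earlier change, T2DM diagnosed outside | Lost; censored at last OGTT | Lost |

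Only the third row threatens the primary analysis. The second and third rows threaten the secondary outcome.

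**Step 2. Reproduce the plan's sample size.** SAP 2.6 says: "A sample size of 1414 women with GDM will provide 90% power" "to detect a relative risk of 0.65". It assumes 20% control incidence at 24 months, a two-sided 5% level, 20% missing outcomes and a chi-square test of two proportions. Allocation is 1:1 (SAP 2.2).

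Intervention rate: 0.65 × 0.20 = 0.13. Mean rate: 0.165.

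n per arm = [1.960 √(2 × 0.165 × 0.835) + 1.2816 √(0.20 × 0.80 + 0.13 × 0.87)]² / 0.07² = 589 after rounding up.

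Total 2 × 589 = 1178, and 1178 × 1.2 = 1414 after rounding up. The plan's figure is reproduced exactly.

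**Step 3. Baseline power with 20% missing.** Evaluable per arm: 1414 × 0.8 / 2 = 565.6.

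Power = Φ{[0.07 √565.6 − 1.960 √(2 × 0.165 × 0.835)] / √(0.20 × 0.80 + 0.13 × 0.87)} = Φ(1.217) = 88.8%.

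Expected events: 565.6 × (0.20 + 0.13) ≈ 187. If every documented interim diagnosis counts, these figures stand.

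**Step 4. Equal loss of a share f of primary events.** The documents give no value for f, so this range is an assumption. Both rates are multiplied by (1 − f) and step 3 is repeated.

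| f | Control | Intervention | Events | Power |
|---|---|---|---|---|
| 0 | 0.200 | 0.130 | 187 | 88.8% |
| 5% | 0.190 | 0.1235 | 177 | 86.9% |
| 10% | 0.180 | 0.117 | 168 | 84.7% |
| 20% | 0.160 | 0.104 | 149 | 79.5% |

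**Step 5. Unequal loss, true relative risk 0.65.** The splits are again assumed.

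- 10% lost in control, 20% in intervention: (0.13 × 0.8) / (0.20 × 0.9) = 0.104 / 0.180 = 0.58. The benefit is exaggerated.
- 20% lost in control, 10% in intervention: (0.13 × 0.9) / (0.20 × 0.8) = 0.117 / 0.160 = 0.73. The benefit is diluted, and power falls to about 55%.

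Steps 3 to 5 use the two-proportion test behind the plan's sample size, not the Cox model of the primary analysis.

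**The case against.** The strongest reply is that a reader might infer a settled rule that women who develop T2DM between visits are never counted, and that the documents do not state one. Four parts of that reply have force.

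- **The word is ambiguous.** In 5.1.4 it follows the statement that follow-up ends, so it may mean only that data collection stops once the event has happened. The outcome window, the demand for confirmatory documents, the silence of protocol 3.6 on T2DM, and the SAP's limiting of last-OGTT censoring to women without an event all fit that reading. It remains possible, but nothing states it. Whether the woman has an event is the very thing left open, and 3.6 uses the word in its ordinary survival sense.
- **Some outside results could qualify.** The cut-offs in SAP 4.9 do not require a study-performed test, so a source laboratory report with fasting or post-load values might meet them. A diagnosis documented by HbA1c or a clinician's record would not. The OGTT-only label in Table 8 mainly contrasts with the HbA1c/FBG analysis and does not address documented diagnoses.
- **The sensitivity analysis may or may not find her.** It would be too strong to say that SAP 4.9.6 certainly misses these women. HbA1c at Months 6, 18 and 30 carries no exemption for interim T2DM, and SAP 3.5 expects an EOS visit at early termination. Against that, 5.1.4 ends follow-up, 5.1.5 asks for HbA1c only if no interim diagnosis was made, and 4.9.6 does not mention outside diagnoses.
- **The size is assumed.** Events on study OGTTs, including those prompted by HbA1c, are safe on any reading. The exposed share may be small.

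These points narrow the group and the certainty. They do not supply the missing rule.

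**Conclusion.** The text as written conflicts with the primary outcome, and this should be resolved before analysis. Followed literally, it drops a component of that outcome by informative censoring for women whose first recorded worsening is a T2DM diagnosis outside a study OGTT, and it drops the T2DM secondary event for every woman diagnosed that way. Under the softer reading the SAP is still incomplete: the two programmers required by SAP 3.12 could arrive at different event counts.

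The effect is modest if losses are few and equal (power 86.9% at 5%). It matters more at 20% (79.5%), or if losses differ by arm (apparent relative risk about 0.58 or 0.73). All of these loss shares are assumptions. The documents do not support a claim about how many events are lost or in which direction the bias would run.

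**What to change.** Before database lock:

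1. In SAP 4.9.2, carried into 4.9.3, 4.9.6 and 4.10, state that an interim T2DM diagnosis confirmed from source documents is an event for the primary outcome (if there was no earlier change) and for the T2DM outcome, dated at the documented diagnosis.
2. State which evidence qualifies, for example whether a diagnosis resting on HbA1c or a clinician's record is accepted.
3. Assign confirmation to the blinded central staff who already perform the source verification in protocol 5.3.
4. Keep the OGTT-only analysis as a sensitivity analysis.
5. Reconcile the censoring sentence in protocol 5.1.4 and the statement on OGTT dependence in 5.3 with this rule. As EOS visits ended on 31 January 2021 and the SAP was finalised on 19 March 2021, this affects the record and the analysis, not conduct.

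The cost is wording plus blinded review of documents the protocol already requires. The downside is that diagnoses made outside the study arise under open-label conditions and may be detected at different rates by arm. The OGTT-only sensitivity analysis helps to check this, and reporting the number of such diagnoses by arm would show how much depends on them.
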